## Abstract

**Background:**

Anaemia and iron deficiency are common complications following post-bariatric abdominoplasty. Given the low oral absorbability of iron resulting from bariatric surgery, it has been hypothesised that postoperative intravenously administered iron supplementation could be used to treat anaemia and to prevent the development of iron deficiency in these patients.

**Methods/Design:**

In this multicentre open-label randomised clinical trial, 56 adult women undergoing post-bariatric anchor-line abdominoplasty will be allocated at a ratio of 1:1 for postoperative supplementation with two intravenously administered applications of 200 mg of iron saccharate or postoperative supplementation with 100 mg of iron polymaltose complex administered orally, twice a day for 8 weeks. The primary outcome is the difference in mean haemoglobin levels between the two groups at eight postoperative weeks. Secondary outcomes evaluated at one, four and eight postoperative weeks include iron profile, reticulocyte count, overall quality of life measured using the Short-Form 36 Health Survey (SF-36) questionnaire, fatigue measured using the Functional Assessment of Chronic Illness Therapy – Fatigue (FACIT-F), adverse effects and postoperative complications.

**Discussion:**

This randomised clinical trial aims to evaluate the haematopoietic effectiveness of intravenously administered iron supplementation in patients undergoing post-bariatric abdominoplasty. A more effective recovery of haemoglobin levels could help improve the patients’ quality of life and could provide an improved haematological status in preparation for the subsequent and frequent plastic surgeries these patients undergo.

**Trial registration:**

Clinicaltrials.gov Identifier: NCT01857011 (8 May 2013), Universal Trial Number U111-1169-6223, Brazilian Clinical Trials Registry (REBEC): RBR-2JGRKQ.

## Background

The increasing prevalence of overweight and obesity in many countries has been described as a global pandemic. The number of overweight and obese individuals has increased from 857 million in 1980 to 2.1 billion worldwide in 2013 [1]. The proportion of adults with body mass indexes (BMIs) above 25 kg/m^2^ has increased between 1980 and 2013 from 28.8 to 36.9 % in men and from 29.8 to 38 % in women [1]. Obesity is associated with increased risk of type 2 diabetes, hypertension, dyslipidaemia, cardiovascular diseases, some types of cancer and mortality [2]. Overweight and obesity were estimated to have caused 3 to 4 million deaths worldwide in 2010, constituting the sixth most important risk factor for disease development worldwide [3].

Treatment options for obesity include different non-surgical treatments and bariatric surgery. Compared to non-surgical treatment, bariatric surgery results in greater weight loss and an increase in the remission rate of type 2 diabetes and metabolic syndrome [2]. However, even though patients undergoing bariatric surgery successfully lose weight, 96 % of patients develop a number of body-contouring deformities caused by excess skin and residual fat deposits [4, 5].

In addition to causing intertrigo and hygiene and mobility difficulties, skin deformities have the potential to affect body image, self-esteem and quality of life [6]. Of the body regions that develop deformities, patients tend to complain the most about the abdomen [7]. After significant weight loss, 75 % of female patients wish to perform body-contouring surgery [5, 8].

However, post-bariatric patients are 60–87 % more susceptible to complications associated with body-contouring surgery compared to non-bariatric patients [9]. Dietary deficiencies are common, with 51.3 % of patients developing iron deficiency and a 36 % prevalence of anaemia [10, 11]. The primary causes of these conditions are reduction in iron intake, gastric acid secretion and contact of food with the iron absorption areas of the duodenal and jejunal segments separated from the gastrointestinal tract as a result of bariatric surgery [12].

During body-contouring surgery, such as post-bariatric abdominoplasty, large areas of subcutaneous tissue and highly vascularised skin are removed and may result in considerable blood loss. Two months after surgery, patients normally still have not returned to preoperative haemoglobin (Hb) levels, and 45 % develop severe iron deficiency [13].

Anaemia is the second most common complication during the postoperative period following post-bariatric abdominoplasty, [7] and these patients have a higher indication for blood transfusion [14]. However, observational studies have found an association between blood transfusion and higher comorbidity and mortality [15–17], and in patients undergoing post-bariatric abdominoplasty, transfusions are associated with a two-fold higher complication rate and longer hospital stays [18].

Moreover, in surgical patients, even low levels of anaemia have been associated with adverse outcomes [19–22]. The recovery of Hb levels is considered an important factor in the postoperative recovery of patients [23], especially in post-bariatric patients, because they are often subjected to additional surgical procedures to treat breast, thigh and arm deformities over relatively short periods of time [24]. In addition, several studies have found that iron deficiency, even in non-anaemic patients, can cause symptoms of fatigue; correcting this deficiency helps improve this symptom [25–27].

Iron supplementation can be administered either orally or parenterally; however, intravenous administration is five-fold more effective in inducing an erythropoietic response after significant blood loss [28]. In addition, orally administered iron can induce side effects such as gastrointestinal symptoms, jeopardising adherence to treatment [29]. Moreover, adverse effects caused by the use of intravenously administered iron, with the exception of high-molecular-weight iron dextran, are rare [30]. Observational studies on orthopaedic surgery [31], digestive tract surgery [32], postpartum haemorrhage [33] and renal transplantation [34, 35] have demonstrated the efficacy of intravenously administered iron in optimising the recovery of Hb levels.

However, a narrative review analysed the results of four randomised controlled trials that evaluated the impact of the use of intravenously administered iron on the perioperative status of cardiac and orthopaedic surgical patients and found that there were no benefits in the recovery of Hb levels or reductions in the number of blood transfusions [36]. In turn, a systematic review evaluated the effects of iron in anaemic patients without chronic kidney disease and observed higher Hb levels with intravenous administration of iron compared to oral administration, but without clinical benefit in terms of reducing blood transfusions or improving quality of life [37]. None of these reviews included patients undergoing post-bariatric surgery. Due to the difficulty in absorbing iron orally and their low levels of stored iron [10], there is the possibility that intravenously administered iron supplementation can result in a better recovery of Hb levels, a decrease in iron deficiency and, consequently, improvements in the patients’ quality of life [13, 38–40].

### Objectives

#### Primary objective

To assess whether iron saccharate supplementation intravenously administered in two 200-mg doses during the perioperative period of post-bariatric anchor-line abdominoplasty results in an increase in Hb levels in the eighth postoperative week (study group) compared to orally administered iron supplementation (control group).

#### Secondary objectives

To investigate whether the use of intravenously administered iron has beneficial effects on other haematological variables, iron profile, transfusion rate, quality of life and clinical outcomes.

## Methods/Design

### Trial design

This is a parallel, superiority, randomised controlled clinical trial with an allocation ratio of 1:1 (Table 1).

**Table 1 Tab1:** World Health Organisation (WHO) trial registration data set

Primary registry and trial identifying number	NCT01857011
Date of registration in primary registry	8 May 2013
Secondary identifying numbers	U1111-1169-6223, Brazilian Clinical Trials Registry (REBEC): RBR-2JGRKQ
Source of monetary or material support	São Paulo Research Foundation (Fundação de Amparo à Pesquisa do Estado de São Paulo – FAPESP), grant #2014/07710-6
Primary sponsor	Federal University of São Paulo
Secondary sponsor	Instituto de Assistência Médica ao Servidor Público Estadual (IAMSPE)
Contact for public queries	[name] ([contact])
Contact for scientific queries	[name] ([contact]
Public title	Iron Supplementation for the Treatment of Acute Anaemia After Postbariatric Tummy Tuck
Scientific title	Postoperative intravenously administered iron sucrose 200 mg administered twice or postoperative orally administered iron for the treatment of post-bariatric abdominoplasty anaemia (ISAPA): a randomised controlled trial
Countries of recruitment	Brazil
Health conditions or problems studied	Postoperative anaemia, iron deficiency
Interventions	Study group: administration of 200 mg of iron sulphate intravenously after post-bariatric abdominoplasty, immediately after the operation and on the first postoperative day
	Control group: ferrous sulphate supplementation orally administered postoperatively at a dose of 1 tablet of 100 mg 12/12 h for 8 weeks.
Key inclusion and exclusion criteria	Inclusion criteria: women; 18 to 55 years old; previous bariatric surgery; body mass index (BMI) less than 32 kg/m^2^; stability of weight loss for at least 6 months
	Exclusion criteria: smoking; cholelithiasis demonstrated by ultrasound; uncontrolled systemic diseases; bone marrow diseases; haematological disorders; presence of renal or hepatic insufficiency; acute infection; prior use of intravenously administered iron in the last 3 months; haemoglobin level less than 11.5 g/dL; ferritin level less than 11 ng/mL or greater than 100 ng/mL; transferrin saturation index below 20 % or exceeding 50 %; vitamin B_12_ level less than 210 pg/mL; folic acid level less than 3.3 ng/mL; albumin level less than 3 g/dL; C-reactive protein greater than 5 mg/L; mean corpuscular volume less than 80 fL
Study type	Interventional
	Allocation: randomised
	Masking: unblinded
	Assignment: parallel
	Purpose: treatment
	Phase: not applicable
Date of first enrolment	April 2014
Target sample size	56
Recruitment status	Recruiting
Primary outcome	Haemoglobin level increase in the eighth week of postoperative abdominoplasty after bariatric surgery, measured by automated haematology counter in g/dL
Key secondary outcomes	Presence of iron deficiency assessed by serum ferritin, postoperative haemoglobin levels, fatigue measured by the Functional Assessment of Chronic Illness Therapy – Fatigue (FACIT-F) questionnaire, quality of life measured by the Short-Form 36 Health Survey (SF-36), adverse events, surgical complications. Timepoints: 1, 4 and 8 postoperative weeks

### Research ethics approval

This protocol was approved by the Research Ethics Committee of The Federal University of São Paulo (CEP UNIFESP) and is registered on the Brazil Platform under Presentation Certificate for Ethics Assessment (Certificado de Apresentação para Apreciação Ética – CAAE) number 11904213.3.1001.5505.

### Consent

The relevant information from this study will be provided to all patients in an understandable way. Patients will have the opportunity to have their questions answered and will provide their consent by signing the free and informed consent form.

### Methods: participants, interventions and outcomes

#### Study setting

The study is being conducted in Brazil, in the urban area of São Paulo city in two hospitals: Hospital São Paulo and Hospital do Servidor Público Estadual (State’s Civil Servants’ Hospital).

### Eligibility criteria

Patients who meet the inclusion and non-inclusion criteria, and provide their consent by signing an informed consent form, are eligible to the study.

### Inclusion criteria

Women, between 18 and 55 years of age, formerly obese patients treated with bariatric surgery using the vertical banded gastroplasty technique with Roux-en-Y gastric bypass by laparotomy, grade III deformity of the abdominal wall using the Pittsburgh rating scale [41], pre-bariatric BMI between 35 and 70 kg/m^2^ and post-bariatric BMI below 32 kg/m^2^ with stabilised weight loss for at least 6 months.

### Non-inclusion criteria

Illiteracy, tobacco use, cholelithiasis shown on ultrasound, uncontrolled systemic diseases, bone marrow diseases, haematological disorders, kidney or liver failure, acute infection, use of intravenously administered iron in the previous 3 months, prior anaphylactoid reaction with the use of intravenously administered iron, Hb levels less than 11.5 g/dL, ferritin levels less than 11 ng/mL or greater than 100 ng/mL, transferrin saturation index (TSI) greater than 50 % or less than 16 %, vitamin B_12_ levels less than 210 pg/mL, folic acid levels less than 3.3 ng/mL, albumin levels less than 3 g/dL, ultrasensitive C-reactive protein (CRP) levels greater than 5 mg/L, and mean corpuscular volume less than 80 fL.

### Exclusion criteria

The exclusion criteria include major intraoperative haemorrhaging with hemodynamic instability or haematoma formation requiring drainage in the operating room.

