#### Surgical complications

Postoperative complications, divided into systemic and local, are evaluated over the 8 weeks of postoperative follow-up, and their percentages are compared between the study and control groups. The following complications are considered systemic: the need for hospital readmission, postoperative blood loss with an indication for blood transfusion, deep vein thrombosis (diagnosed by ultrasound examination), pulmonary embolism (diagnosed using an angiographic examination) and death.

The following complications are considered local: seroma (accumulation of serous subcutaneous fluid evident upon physical examination after removing the drain and following at least one aspiration); haematoma (accumulation of haematic subcutaneous fluid evident upon physical examination after removing the drain and following at least one aspiration); wound infection (based on the definition established by the Centers for Disease Control and Prevention (CDC) [55]); wound dehiscence (defined as separation of the wound margins requiring medical or surgical treatment [56]); and necrosis (defined by the presence of devitalised tissue that extends through the full thickness of the skin, requiring surgical debridement).

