### Methods – assignment of interventions

#### Allocation – sequence generation

The patients are allocated to the study or control group at a ratio of 1:1 using a computer-generated randomiser (http://www.randomization.com) with fixed block sizes. The block sizes are kept confidential.

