#### Allocation: implementation

A surgical team member who did not participate in the recruitment of patients generated the allocation sequence and maintained the allocation concealment. The researchers responsible for recruitment did not receive any information regarding the patient allocation groups. The sequentially numbered envelopes remained stored with the surgical team member throughout the study. Prior to the post-bariatric abdominoplasty surgery, the surgeon wrote the name of the patient on the envelope that corresponded to the numerical sequence of the research. At the end of the surgery, the envelope was opened, revealing the research group to which the patient belonged.

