### Statistical methods – analysis population and missing data

Data analysis will be performed based on the original allocation of all patients as defined by randomisation, regardless of the degree of adherence to the protocol (intention-to-treat principle).

With respect to missing data, the amount thereof, their patterns and variables associated with omission will define the most appropriate technique to be used in the processing of such data, whether in the primary analysis or the sensitivity analysis. For primary analyses, methods will be used that make use of all available data, such as multiple imputations. To reduce the presence of incomplete data and attrition bias, the need to discontinue the allocated treatment will be considered as treatment failure.

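### The haematoma exclusion has no time limit, so it can remove a patient after her arm is known, against the as-randomised analysis and the haematoma comparison

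*Protocol article*

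**What the plan says.** The protocol article separates non-inclusion criteria, which are checked before surgery, from Exclusion criteria. The latter consist only of "major intraoperative haemorrhaging with hemodynamic instability or haematoma formation requiring drainage in the operating room".

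Under Allocation: implementation, before the operation "the surgeon wrote the name of the patient on the envelope that corresponded to the numerical sequence of the research". Then: "At the end of the surgery, the envelope was opened, revealing the research group to which the patient belonged". Under Interventions, the first intravenous dose is given in the immediate postoperative period and the second on the following day. Under Blinding, patients and researchers are unblinded; the exception is the surgeon who assesses local complications.

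The section on analysis population and missing data states: "Data analysis will be performed based on the original allocation of all patients as defined by randomisation, regardless of the degree of adherence".

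Under Surgical complications, complications "are evaluated over the 8 weeks of postoperative follow-up, and their percentages are compared between the study and control groups". The local ones include "haematoma (accumulation of haematic subcutaneous fluid evident upon physical examination after removing the drain and following at least one aspiration").

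**The concern.** An exclusion made after allocation is known, because of an event bound up with the outcome, loses the protection of randomisation. A haematoma that needs theatre drainage is such an event. It involves blood loss, the primary outcome is haemoglobin at week 8, and haematoma is itself a compared complication.

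Two results are at stake. The primary comparison could lose patients likely to have low haemoglobin, by a decision taken with the arm known. The complication comparison could count the milder haematomas and omit those that went to theatre. If follow-up stops at exclusion, neither loss can be repaired at analysis.

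**Working it through.** **Order of events in the protocol article**

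1. Before surgery: the patient's name goes on the next numbered envelope, which stays sealed.
2. During surgery: the haemorrhage criterion can be met. The arm is unknown and no study iron has been given.
3. End of surgery: the envelope is opened.
4. Immediate postoperative period and day 1: intravenous iron in the study arm.
5. Up to week 8: complications and haemoglobin are recorded.

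The haemorrhage criterion can operate only at step 2. The haematoma criterion has no stated time and can operate at steps 2, 4 or 5. If it operates at step 4 or 5, the exclusion comes after randomisation on any definition of that moment, and the arm is known to patients and researchers.

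**Against the analysis rule.** All patients are to be analysed as randomised. The article does not say whether a patient who meets an exclusion criterion after opening is followed up or analysed. The treatment-failure rule covers discontinuation of allocated treatment, which is a different matter.

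**Against the haematoma outcome.** The definition needs a collection found after drain removal and at least one aspiration. A haematoma taken straight to theatre, or drained there while the suction drains are still in, does not meet it even if the patient is kept.

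**Planned size, reproduced first.** Inputs from Sample size: difference 1.5 g/dL, SD 1.84, two-sided 0.05, power 80 %, loss 10 %.

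- Normal approximation: n = 2 × (1.96 + 0.84)² × 1.84² / 1.5² = 23.6, so 24 per arm.
- t-test version: 24.6, so 25 per arm; 25 / 0.9 = 27.8, so 28 per arm and 56 in total.

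The stated 56 is reproduced and is not in dispute. The section mentions no allowance for exclusions.

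**How many patients.** No event rate is given, so the rates below are assumptions. Expected number = 56 × rate. Chance of at least one = 1 − (1 − rate)^56. Power is for the t-test with 28 × 0.9 × (1 − rate) per arm.

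| Assumed rate | Expected of 56 | Chance of at least one | Power |
|---|---|---|---|
| 0 % | 0 | 0 % | 80.9 % |
| 2 % | 1.1 | 68 % | 80.1 % |
| 5 % | 2.8 | 94 % | 78.8 % |
| 10 % | 5.6 | 99.7 % | 76.5 % |

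**Possible shift in one arm mean (illustration only).** If k of 28 patients lie d g/dL below the rest and are removed, the arm mean rises by k × d / 28.

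- k = 1, d = 1: 0.04 g/dL
- k = 2, d = 2: 0.14 g/dL
- k = 3, d = 2: 0.21 g/dL

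For scale, the standard error of the difference with 25 per arm is 1.84 × √(2/25) = 0.52 g/dL. The middle case is 0.14 / 0.52 = 0.27 of a standard error and 0.14 / 1.5 = about 10 % of the target difference. Both k and d are assumed, and so is the removal from one arm only.

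**The case against.** Several points on the other side stand.

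- **Intraoperative haemorrhage.** A reader might infer that unblinded staff can remove bleeding patients under both criteria. The documents do not support this for haemorrhage: it is decided while the envelope is sealed and before study iron. A vacated envelope falls on either arm by chance. It can disturb a fixed block and the count of patients, but it does not bias the comparison.
- **Timing of the haematoma.** A reader might take the criterion as expressly postoperative. It is not; it is untimed, and could have been meant for events before the patient leaves theatre. That narrower meaning is not written down, and nothing rules out the later one.
- **The analysis rule.** The as-randomised rule could be read as governing, so that such patients stay in. The conflict arises only if exclusion means removal from follow-up or analysis. The article does not define it, and the flow diagram and the full protocol, which are not at hand, may do so.
- **Serious haematomas.** A reader might infer that their reported rate would be zero by construction. That goes too far. The definition does not bar a collection that is aspirated and later drained in theatre, and readmission and blood loss with an indication for transfusion are counted separately. These help only for patients who stay in the analysis.
- **Size.** A reader might treat 0.14 g/dL as the bias. The event rate, the haemoglobin deficit and the 2-versus-0 split are all assumed, and no passage says that the iron route affects bleeding.

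The blinded assessor of local complications is a real safeguard for that outcome, but the article does not give this surgeon the exclusion decision.

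**Conclusion.** The point holds for the haematoma criterion. As written, it permits a post-randomisation exclusion on an outcome-related event with the arm known. Applied in that way, it conflicts with the as-randomised analysis and takes theatre-drained haematomas out of the complication comparison. For haemorrhage during surgery, only patient accounting and block balance are at issue.

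The size of any bias is unknown because no event rate is given. At assumed rates of 2 to 10 %, about 1 to 6 of 56 patients are affected and power falls by about 1 to 4 percentage points. Power is therefore a minor matter; selection and under-counting of haematomas are the reason to act. The conclusion assumes that exclusion means leaving follow-up or analysis, and that the haematoma criterion is not confined to the time before opening. The article states neither, and the amendment should settle both.

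**What to change.** Reconcile Exclusion criteria, Surgical complications, Allocation: implementation, and the analysis population section in one amendment:

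1. Define randomisation as the opening of the envelope, and limit both exclusion criteria to events before that moment.
2. Follow up every patient with a later event to week 8 and analyse her in her allocated arm.
3. Count any haematoma drained in the operating room as a haematoma complication, whether or not it was aspirated and whether or not the drain was still in place.
4. Report all exclusions and all used envelopes, with timing relative to opening and the arm where it was revealed. Include any among the 19 patients operated on by August 2015.

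The name can still be written on the envelope before surgery. Moving that step to the end of the operation is not needed, because exclusions before opening are already blind to arm.

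The cost is a short text change with ethics committee approval, which the article already requires for amendments. Treatment is unchanged. The one small downside is slightly more variable haemoglobin from the patients who are kept.
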